### 9.1.10 Adverse Event Assessment Diagram

[figure not shown]

The ITCC will distribute the SAEs to the relevant parties and committees per ITCC SOP 5.17 Adverse Event Reporting and in accordance with state and territory guidelines, the requirements of the approving central Ethics Committee and local governance offices and the Medical Monitor. In addition, events deemed to be both serious and unexpected, and related to the study intervention, will be reported by the ITCC to the Therapeutic Goods Administration (TGA) via their website (<https://aems.tga.gov.au/>). The online reporting is to be used to enable reporting between sites, local forms of reporting are also to be used for reporting to local sites.

### **9.1.11      *Follow-up of AEs and SAEs***

After the initial report, investigators are required to follow-up each AE and provide further information both to the ITCC and the hospital HREC and/or RGO. All events reported as ongoing are to be reviewed at subsequent visits or appointments in order to report progress and resolution. All events are to be followed until:

- resolution;
- the condition of the participant stabilises;
- the event can be explained;
- the participant is lost to follow-up; or
- death.

Reports are to contain details of follow-up investigations, result reports or reports from other consultations, and are to be updated in a follow-up report to the ITCC and the approving HREC and/or RGO.

### **9.1.12      *Post study AEs and SAEs***

A post study event is defined as any event that occurs outside of the time period described in section 9.1.8 of the protocol. Investigators are required to report any events they become aware of if:

- the event occurs at any time after study participation has ceased; and
- the event is assessed as being reasonably related to the study intervention.

Investigators are not obliged to actively seek events that occur after the study period defined in 9.1.8. Date of death will be required for all participants regardless of when they withdrew from the study up to the dataset being closed.

## **9.2      *Auditing/Monitoring***

### **9.2.1      *Peer review and site visits***

Each study site will be reviewed by the ITCC Project Officer (or delegate) prior to recruitment commencement, when the site coordinator and study nurse will be assessed as appropriate, and trained in the data collection, data entry, and filing and other trial procedures in order to comply with Good Clinical Practice (Site Initiation

Visit, SIV). The assessment will be recorded and a copy sent to the study site. Ongoing peer review will be undertaken via regular study nurse telephone links and ongoing assessment by the study investigator.

### **9.2.2 Pharmacy training**

At the site initiation visit, the third party pharmacy will be visited or telephoned by the National Project Officer (ITCC)/delegate. At this time, the pharmacy staff will be trained on the pharmacy procedures, the protocol will be reviewed in detail and a pharmacy manual provided. The manual has been prepared with the input and advice of experienced trial pharmacists prior to finalisation.

### **9.2.3 Monitoring visits**

Internal monitoring of the study is described in detail in the Monitoring SOP (5.18, Monitoring).

Briefly, each study site will be monitored by staff from the ITCC at initiation, mid-recruitment and study closure where all study procedures, recording, reporting and maintenance will be checked, including the pharmacy records. This will include data quality, protocol violations, AE reporting, participant existence and eligibility, and other aspects to determine Good Clinical Practice compliance. Monitoring for this study will take a pragmatic and risk-based approach, where on-site visits will be undertaken based on the outcomes of continuous central remote monitoring of recruitment, data quality, compliance, protocol violations and direct communications.

## **9.3 Quality control**

### **9.3.1 Training procedures:**

The following training procedures will be conducted to ensure quality control. Competency will be recorded at the ITCC with a copy of the training records filed at each study site.

| Person trained           | Description         | Assessed by                                  |
|---------------------------------|----------------------------|-----------------------------------------------------|
| All site staff                  | ICH GCP training           | National manager (PaCCSC/CST)                       |
| Study nurse                     | Blood sampling             | Pathology department                                |
| Study nurse                     | Eligibility assessment     | Site investigator                                   |
| Study nurse                     | Consent procedure          | Study coordinator                                   |
| Investigator, sub investigators | ICH GCP training; Protocol | National manager (PaCCSC/CST)
Chief investigator |
| Study nurse, investigators      | Data management            | National manager (PaCCSC/CST)                       |

| Person trained                  | Description                                      | Assessed by                                         |
|---------------------------------|--------------------------------------------------|-----------------------------------------------------|
| Medical staff                   | Prescription                                     | Site investigator                                   |
| Clinical trials pharmacist      | Randomisation, medication preparation procedures | National manager (PaCCSC/CST)
Chief investigator |
| Investigator, sub investigators | Safety assessments                               | National manager (PaCCSC/CST)
Chief investigator |

### **9.3.2 Blood collection**

Venous blood samples will be drawn for eligibility screening, baseline and follow-up assessments. Ensuring that the study involves minimal burden to participants is crucial in this study, therefore, in some instances (e.g., if clinical picture has not otherwise changed), blood samples taken as part of diagnosis as well as pre-chemotherapy/radiation therapy can be used for screening. The results will be held in the participant study file as source data. This will be collected as per the site's SOP for venepuncture, with results reviewed and signed off by the Site Investigator or delegated medically trained staff member (such as sub-Investigator).

Each study site will keep a copy of the pathology service guidelines for obtaining, transporting and storing blood samples.

## **9.4 Data Management**

### ***9.4.1 Data handling and record keeping***

The ITCC has a number of Standard Operating Procedure that will apply to all sites for the management of study data. Specifically, the following Standard Operating Procedures (SOPs) apply:

- SOP 5.5.1            Electronic Data Handling
- SOP 5.23.2        CRF completion
- SOP 8.0             Essential documents
- SOP 8.4.1         Archiving of research/project materials
- SOP 8.42           Record destruction

### ***9.4.2 Direct access to source data***

A statement of permission to access source data including medical, health and mental health records for regulatory and audit purposes is included within the participant consent form with explicit explanation about this given as part of the consent process. Specifically, access will be required by study staff (including investigators, site coordinators and study nurses), Human Research Ethics Committees (HRECs), Medical Monitor and the ITCC data management team. Increasingly, there is a requirement to make the data available at publication dependent on the journal requirements and this would be done in a summarised and de-identified format. So de-identified data may be made available to bona fide researchers for meta-analysis and where requested by journals for publication purposes. Regulatory authorities may require use of the data for subsidy applications. In addition, the aggregated study data will be used to inform the next phase of the study. Any future use of the study data would be at the discretion of the Sponsor/data custodian.

The Data Collection Worksheets listed below will be provided for data entry into the electronic Case Report Forms (eCRF):

- Eligibility
- Baseline
- Intervention
- Treatment Cessation
- Withdrawal
- Follow-up

***Anamorelin for anorexia, V1.6, 7 April 2022***

- Medical Assessment and Screening Form

### 9.4.3 Data collection

Data will be sourced from the following:

| Measure                                                                               | Source                                          | Completed by:                 |
|---------------------------------------------------------------------------------------|-------------------------------------------------|-------------------------------|
| General demographic details                                                           | Clinical file                                   | Study nurse                   |
| General medical information and Charlson comorbidity                                  | Clinical file/ medical assessment               | Medical officer/ investigator |
| Concurrent medications                                                                | Clinical file                                   | Medical officer               |
| Pathology results                                                                     | Pathology report                                | Pathology service             |
| Vital signs                                                                           | Clinical file                                   | Study nurse                   |
| Patient reported outcomes                                                             | Questionnaires                                  | Participant                   |
| Patient-reported symptom measures;                                                    | Worksheet                                       | Study nurse                   |
| Physical examination                                                                  | Worksheet                                       | Medical officer/ Study nurse  |
| Physiological measures: weight, BMI, BIA, DEXA and CT scans for body composition, ECG | Worksheet/record of BIA, DEXA and CT scans, ECG | Study nurse                   |
| Adherence: medication, physical activity and dietary advice                           | Participant diary                               | Participant                   |
| Adverse events, safety                                                                | Clinical file and Worksheet                     | Study nurse                   |

To assist sites in ensuring that the study data collected are complete and consistent, ITCC develops and provides study specific data collection worksheets for use. The worksheets are designed to capture the required data and to enable smooth data entry in the eCRFs through similar question and response structures, where required data fields are highlighted in order to minimise data entry errors and prevent missing data.

Study data including data collected on paper data collection worksheets will be entered and stored on an electronic database. This web-based data capture system enables the application of data validation rules to ensure that required data is entered or that an annotation is provided to explain any missing data. Validation rules to assist with data checking such as rules that apply to expected visit dates or values that fall within a specified range are also used to flag potential data entry errors in real-time and require an annotation to explain entry of erroneous values. The completion of specific system and data entry training is mandatory for all site staff requiring access to the data capture system as per ITCC SOP 5.5.1 Electronic Data Handling.

#### **9.4.4 Electronic recording**

Study data will be recorded in a number of files for both the administration of the study and collection of participant data.

- A master index (PMI) will contain confidential participant contact information and will be the only link between individual participants and the ID number. This will be an Excel spreadsheet (Master patient index.xls).
- The Data file will be held and administered in the ITCC and will contain all the participant data as downloaded from the eCRFs. This data will then be transferred to the data set for analysis.

#### **9.4.5 Data entry**

Study data will be collected and stored on paper Data Collection Worksheets and then entered onto and managed on REDCap (Research Electronic Data Capture) database or eCRF. The eCRF database will contain the responses to the Data Collection Worksheets, telephone monitoring data and the participant medication use.

Audio data, identified only by study ID will be collected on a digital recording medium and stored temporarily at any of the study or sponsor sites until uploaded to the REDCap database. The original file will then be destroyed.

REDCap is a secure web-based application designed to support data capture for research studies, providing user-friendly web-based case report forms, real-time data entry validation, audit trails and non-identified data export mechanism to common statistical packages. All web-based information transmission in REDCap are protected via Secure Sockets Layer (SSL) encryption (data entry, survey submission, web browsing, etc).

The creator of a REDCap project database may grant other users access to the project and limit those users' privileges as desired. All users are given individual system usernames and passwords. Passwords are at least 9 characters long and have to be alphanumeric. REDCap has an audit trail for all data entry and subsequent alterations to data.

#### **9.4.6 Data querying**

Data will be checked according to ITCC Standard Operating Procedure 5.5.1 Data Handling. eCRF data entry will be checked by a series of programmed checks and listing reviews incorporated into the REDCap interface using validation rules. Queries will be either automatically generated or manually added to the eCRF for resolution by the site. Responses to queries will be entered directly into the eCRF by site staff. RedCAP maintains an audit trail of all queries, responses and data corrections. Quality control audits of all key safety and efficacy data in the database are made prior to locking the database.

#### **9.4.7 Data storage**

All data collected at each site for each participant will be kept in a participant file (identified by ID number only) which will contain the Data Collection Worksheets, any corrected and amended data, copies of AE reports, file notes, consent forms, pathology reports, medication chart etc. All participant files will be securely stored at each study site in a locked area that is only accessible to study staff and away from the administrative files for the study. All scanned CRFs sent to the Trial Coordination Unit will be filed in a password protected network folder, until study archive. All study files will be stored for 15 years.

If it is the site's policy, identifiable data (consent forms, pathology reports, etc.) may be de-identified and filed with the study documents or alternatively can be stored separately from the participant's study file during the recruitment period to further avoid potential re-identification of participants. All participant files will be reconciled and stored along with all study materials – both hard copy and electronic – consistent with ICH GCP R2 and applicable regulations regarding the retention and disposal of participant records.

## 10.0 STATISTICS

### 10.1 Power and sample size

A total of 50 participants with small cell lung cancer will be randomised 1:1 to anamorelin HCl 100 mg or placebo in order to have data at 12 weeks on 40 participants (approximately 20 in each treatment arm). Since this is a feasibility study, it is not required to calculate a fully justified sample size for establishing the efficacy of the intervention. It has been suggested, however, that in feasibility studies, a sample size between 24 and 50 is acceptable. The findings from this study will be used to inform the calculation of a sample size for a future larger scale phase III trial.

Participants discontinued after randomisation will not be replaced.

### 10.2 Alternative hypotheses to be tested

#### Feasibility

There will be adequate recruitment and retention of participants with SCLC and anorexia for the phase II trial.

#### Desirability

Anamorelin will show sufficient clinical signal of difference between the treatment and control arms with acceptable safety measures.

### 10.3 Analysis of primary outcomes

#### Feasibility

*Primary analysis* will be concentrated on the feasibility metrics based on defined thresholds. As this is a feasibility trial, there will be no imputation. Data relating to quantitative variables will be analysed with simple frequencies. Comparison between the intervention and control groups will be compared using appropriate statistical approaches, depending on the nature of the data.

### **Efficacy outcomes**

Changes from baseline to 12 weeks or 24 weeks in each of the secondary endpoints will be calculated. An exploratory analysis of the potential differences between arms will be performed using t-test for continuous normally distributed data or Wilcoxon Test for continuous non-normally distributed data.

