### 4.3 Method of assigning participants to treatment groups

At each site, people referred to the study will be sequentially allocated a unique identification (ID) number. This ID number will be used for all subsequent study documentation for that participant.

Treatment for each participant will be allocated in a 1:1 ratio. Block randomisation will occur in each stratum at each site in randomly assigned blocks of 4 or 8 and will ensure even allocation to each code. Central randomisation will be stratified by limited versus extensive disease and by baseline score of the 5-item Anorexia Symptom Scale Domain from the 12-item FACCT A/CS ( $\leq 10$  vs  $>10$ ). The 5-item from the FACCT A/CS are as follows: *F1. I have a good appetite; F6. My interest in food drops as soon as I try to eat; F7. I have difficulty eating rich or "heavy" foods; F10. When I eat, I seem to get full quickly; F4. Most food tastes unpleasant to me.*

On notification of a participant, the delegated pharmacist at a third party pharmacy will email the ITCC Central Randomisation Service ([contact]) providing the required registration details and receive the treatment allocation via reply email. This allocation will be printed or saved electronically into the pharmacy records. The participant ID, allocation code, dates of request, preparation, and dispensing will be recorded in a log maintained by the pharmacist and supplied to the central registry on each randomisation.

Participant randomisation will be registered with the IMPACCT Trials Coordination Centre (ITCC). In summary, the procedure outlines that, on randomisation of a participant, the third party pharmacy is to email a notification to the ITCC. This notice will be monitored alongside the participant eligibility as entered onto the electronic Case Report Form (eCRF) from the Eligibility data collection worksheet.

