## 4.8 Cessation of study drug/intervention

Treatment may be ceased for one of the reasons listed below. A description of the reason behind ceasing the drug will be recorded in the medical record or clinical file as per the site's SOP.

- Reached primary endpoint (12/ 24 weeks).
- Participant request.
- Insertion of tube feeding or parenteral nutrition.

- Unacceptable side effects from study medications (defined by National Cancer Institute Common Criteria for Adverse Events; NCI-CTCAE version 5.0) of grade 3 not resolving with appropriate treatment or any grade 4 or 5 toxicities.
- An AE occurs that, in the opinion of the Investigator, makes it unsafe for the participant to continue in the study.
- Participants who in the opinion of the Investigator are not well enough to continue the study (specific reasons for cessation need to be documented in the data collection worksheet and electronic Case Report Form – eCRF).
- It is inappropriate to continue the study medicine for whatever reason.
- The participant or proxy withdraws their consent for continued administration of the study medication, with or without withdrawing consent from study and all protocol-specified assessments and follow-up procedures.
- The participant dies.
- The participant is lost to follow-ups.
- The Investigator, for any reason, terminates the entire study, or terminates the study for that participant; or the attending physician requests that the participant be withdrawn for any medical reason.
- The Sponsor or the Regulatory Authorities or the Ethics Committee(s), for any reason, terminates the entire study, or terminates the study for this trial site or participant.

If a participant prematurely discontinues treatment with anamorelin/placebo at any time prior to completing the 12-week visit, the Investigator must try his/her best to contact the person for scheduled visits. Every effort will be made to collect data from the protocol-specified assessments. Participants will be asked to continue to participate in the study and complete planned visits up to Week 12 even if they have permanently discontinued treatment with anamorelin/placebo (“retrieved dropout” approach). If participants discontinue study participation at any time, they will be asked if they can participate in one final clinical visit and whether they would participate in a follow-up telephone call seven days later.

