### **5.1.3 Efficacy (for clinical assessments)**

1. Change in the 5-item Anorexia Symptom Scale Domain from the 12-item Functional Assessment of Anorexia Cachexia Treatment (FAACT, anorexia/cachexia – A/CS) scale by arm from baseline to week 12.
2. Rates of *on time, on dose* completion of any administered chemotherapy and/or radiotherapy for SCLC during the duration of the study.

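### The only efficacy tests the plan names are unadjusted tests on change from baseline; adjusting for the baseline score already collected would tighten the estimate at no data cost

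*Supplement*

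**What the plan says.** Under Efficacy outcomes in section 10.3, the protocol states: "Changes from baseline to 12 weeks or 24 weeks in each of the secondary endpoints will be calculated". It continues: "An exploratory analysis of the potential differences between arms will be performed". The comparison is to be "performed using t-test for continuous normally distributed data or Wilcoxon Test for continuous non-normally distributed data". The Trial Summary repeats this. Under Feasibility in the same section, two general statements apply: "Comparison between the intervention and control groups will be compared using appropriate statistical approaches, depending on the nature of the data" and "As this is a feasibility trial, there will be no imputation".

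Section 5.1.3 lists the first primary efficacy measure: "Change in the 5-item Anorexia Symptom Scale Domain from the 12-item Functional Assessment of Anorexia Cachexia Treatment", from baseline to Week 12. Section 10.3 does not name a test for it.

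The design supplies information that these tests do not use:

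- Section 4.3: "Central randomisation will be stratified by limited versus extensive disease and by baseline score of the 5-item Anorexia Symptom Scale Domain", with the score split at 10.
- Section 6.7 and Table 6-1: FAACT is completed at screening, baseline and Weeks 4, 8 and 12, and at Weeks 18 and 24 in the extension.
- Section 4.8: participants who stop study drug are asked to "complete planned visits up to Week 12 even if they have permanently discontinued treatment with anamorelin/placebo".

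Section 10.1 randomises 50 to obtain Week 12 data on 40, about 20 per arm. It gives no SD, correlation, effect size or precision target. Only a protocol is shown; there is no separate analysis plan.

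**The concern.** A two-sample test on change subtracts the whole baseline value from the follow-up value. That is the most efficient use of baseline only when follow-up rises one-for-one with baseline. At a lower correlation, subtraction adds baseline noise to the outcome, whereas ANCOVA estimates how much of the baseline to remove. With no imputation, a Week 12 two-sample test also uses only participants with a Week 12 value, even where Week 4 and Week 8 scores exist.

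Two decisions lean on this comparison. Section 5.1.2 makes desirability a primary outcome and ties it partly to whether the efficacy signal points to a clinically meaningful difference. Section 10.1 says the findings will feed the phase III sample size. With about 20 per arm, precision is scarce. A Wilcoxon p-value also does not give a mean difference that can be set against a minimum important difference.

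**Working it through.** **Inputs.** From section 10.1: 50 randomised, 40 with Week 12 data, 20 per arm. From section 10.3: an unadjusted test on change. Assumed: correlation rho between baseline and Week 12 scores (0.3, 0.5 and 0.7 shown), and equal variance at the two times.

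**Plan's own figure.** The implied loss is 10/50 = 20%, and 40/(1 − 0.20) = 50. The numbers agree, although the plan does not state 20%.

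**Precision.** In units of the score variance, the per-person variance is 2(1 − rho) for change and 1 − rho² for ANCOVA. The ratio is (1 − rho²)/[2(1 − rho)] = (1 + rho)/2. The 95% half-width is 1.96 × √(variance × 2/20), in SDs of the score. The equivalent number is 40/ratio.

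| Assumed rho | Variance ratio | Variance lost | CI width lost | Half-width, change | Half-width, ANCOVA | 40 act like |
|---|---|---|---|---|---|---|
| 0.3 | 0.65 | 35% | 1 − √0.65 = 19% | 0.73 | 0.59 | 61.5 |
| 0.5 | 0.75 | 25% | 1 − √0.75 = 13% | 0.62 | 0.54 | 53.3 |
| 0.7 | 0.85 | 15% | 1 − √0.85 = 8% | 0.48 | 0.44 | 47.1 |

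**Small-sample cost.** Estimating the baseline slope from 40 people multiplies the ANCOVA variance by about 1 + 1/36. The ratios become 0.668, 0.771 and 0.874, so nearly all the gain remains. With this factor the break-even correlation is 2 × 36/37 − 1, about 0.95.

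**Narrowed baseline.** Entry requires a score of 37 or less on the parent 12-item scale (section 3.4.2.1), which may compress the baseline spread. As an assumed illustration, take slope 0.5, residual variance 0.75 and baseline variance halved to 0.5. The change-score variance is then 0.75 + (1 − 0.5)² × 0.5 = 0.875. The ratio is 0.75/0.875 = 0.86, a loss of 14% instead of 25%.

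**Simulation.** 4,000 runs per setting, 25 per arm, 20% dropout completely at random, two correlation patterns. Strata carried no information beyond baseline, and the repeated-measures model was given the true covariance, which flatters it. Variance relative to the change score:

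| Assumed rho | ANCOVA | ANCOVA plus both strata | Repeated measures, Weeks 4, 8, 12 |
|---|---|---|---|
| 0.3 | 0.66–0.67 | 0.70–0.71 | 0.63–0.64 |
| 0.5 | 0.77–0.79 | 0.81–0.84 | 0.71–0.75 |
| 0.7 | 0.86–0.88 | 0.91–0.93 | 0.79–0.83 |

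Most of the gain comes from the continuous baseline score. The interim visits add a little, and uninformative strata take a little back.

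**The case against.** The strongest reply is that this is a feasibility trial. Its primary analysis is the feasibility thresholds, its size is not power-based, and the efficacy comparison is labelled exploratory. Randomisation makes the change-score comparison unbiased, so only efficiency is at issue. That stands, and it limits the weight of the point. It does not remove it, because desirability depends partly on the efficacy signal.

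Several stronger readings are tempting, and the documents do not support them:

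- **That the t-test is prescribed for the primary FAACT endpoint.** The sentence names secondary endpoints, and the wording under Feasibility leaves the method open. It does not exclude ANCOVA. Applying the t-test to FAACT is a reasonable inference, not stated text, and detail may be left to an analysis plan that is not shown.
- **That only treatment completers are analysed.** Section 4.8 plans follow-up to Week 12 after drug is stopped. The analysed set is participants with an observed value.
- **That a quarter of the precision is lost.** That is a variance figure at rho = 0.5, which no section gives. In interval width it is 13%.
- **That omitting the strata is itself costly.** Nothing in the documents shows that disease extent predicts this score beyond baseline, and uninformative strata cost a little at this size.
- **That no effect estimate would be available.** Section 10.3 calculates changes, and section 10.4 promises descriptive statistics for each outcome measure.

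A repeated-measures model is also not free of assumptions. It relies on data missing at random and does not settle what a score means after death, which matters given the short life expectancy described in section 9.1.5.

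**Conclusion.** The point holds as a matter of efficiency. The only tests named are unadjusted tests on change among participants with an observed Week 12 (or 24) value, and the primary FAACT change has no specific method. Leaving out the collected baseline score costs about 15% to 35% of variance, or 8% to 19% of interval width, for rho from 0.7 down to 0.3.

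The range rests on an assumed correlation and equal variances at baseline and Week 12; a compressed baseline makes the loss smaller. The direction is secure unless follow-up rises almost one-for-one with baseline. It would be wrong to infer that the planned comparison is biased or that the trial's conclusions would be invalid. The change is worth making because it sharpens an estimate that informs the desirability judgement and phase III planning.

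**What to change.** In section 10.3 and the matching Trial Summary text, or in an analysis plan:

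1. State that the Week 12 5-item FAACT score will be compared by ANCOVA adjusted for the continuous baseline score, and extend the same method to the other continuous endpoints using their own baseline values. This replaces the choice between t-test and Wilcoxon.
2. Disease extent may be added as a covariate because it is a stratification factor. The continuous baseline score should be used in preference to its split at 10.
3. Report the adjusted mean difference with its 95% confidence interval, and state how many participants per arm contribute.
4. Optionally, add a repeated-measures model for FAACT at Weeks 4, 8 and 12 as a supporting analysis, stating its missing-at-random assumption and how deaths are handled.

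The no-imputation statement can stay. The cost is protocol or analysis-plan wording and light programming, with no new data, visits or participants.
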